### Statistical methods

The main analysis will be run as intent-to-treat analysis (IIT) (within and between groups comparisons at 16 weeks, and the end of treatment) as well as per-protocol analysis (PP; which will exclude participants who had less than 8 sessions – i.e., half of the expected length of the treatment). Primary (OASIS, ODSIS, and CORE-OM) and secondary outcomes (client relevant disorder specific measures; as well as OSSIS, OLSIS, and OFSIS) will be analysed using repeated measures ANOVAs at 16 weeks and at the end of treatment. Effects will be tested at the 0.05 level. After 16 weeks, participants from the wait-list will be provided with the active treatment, and pre-post and 6 months follow-up will be assessed for the collated group. Analysis will also be conducted to determine the proportion of participants who achieved clinically significant change and reliable improvement (
Jacobson & Truax, 1991) at the end of the treatment, at 16 weeks, and at 6 months follow-up. The size of the within-group effects (Cohen’s
*d*) will be calculated. The magnitude of between-group effects at 16 weeks and at the end of treatment will also be established.

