The model of transformation proposes that the client is first facilitated to use internal resources to cope with symptoms, and to recognize his or her own agency in contributing to the development of these symptoms. The client is then helped to develop a capacity to access and tolerate the specific painful feelings underlying these symptoms, and by doing so, to identify and articulate the unmet needs embedded in these painful feelings. This in turn allows for a process of emotional transformation whereby the client is ultimately helped to transform maladaptive emotions through the generation of adaptive emotional responses (e.g., compassion or protective anger) to identified unmet emotional needs. Therapy thus focuses on (1) a firm case conceptualization; (2) the provision of an emotionally attuned and compassionate therapeutic relationship; (3) the overcoming of symptoms (e.g., ruminations, worries, obsessions, flashbacks, overwhelming distress) through increasing internal coping resources and through experiential tasks which highlight both the function and cost of the emotional processes which bring about and maintain symptoms; and (4) the transformation of chronic underlying painful maladaptive emotions through experiential tasks that activate maladaptive emotions (loneliness/sadness, shame, fear), bring to awareness the unmet needs (for connection, validation and protection) embedded in those painful emotions, and facilitate the generation of adaptive emotional responses (e.g., compassion and protective anger) to those unmet needs.

Therapy will last 16 to 20 sessions. Therapists will be instructed to finish therapy at session 16, but will have flexibility based on their clinical judgement to extend therapy to a maximum of 20 sessions. This flexible ending is based on learning from a previous project [
[name] *et al.*, 2017], in which it became apparent that some clients needed more than the initially anticipated number of sessions, but benefited significantly from the addition of a relatively small number of sessions. We propose that therapists extend therapy for up to an additional four sessions if (1) the client continues to be clinically distressed (e.g., the therapist can use a formal assessment such as the OASIS and ODSIS, which is collected as part of the study) and (2) the client expresses an explicit wish to continue with therapy for this duration.

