The delayed intervention, offered to wait-list participants at 16 weeks, will be delivered as per the active intervention described above.

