Barlow *et al.*, 2017b). These three experimental measures will be: the Overall Shame Severity and Impairment Scale (OSSIS), the Overall Loneliness Severity and Impairment Scale (OLSIS), and the Overall Fear Severity and Impairment Scale (OFSIS). These scales should tap onto participants’ underlying chronic painful feelings of shame, loneliness/sadness, and fear (see below). Initially, all three measures will be administered to all participants. Subsequently only measures on which a participant scored ≥8 (this tentative cut-off is based on the wording of the anchors and cut-offs for OASIS and ODSIS) will be used for that particular individual. At the end of active treatment, participants will be also interviewed using the Client Change Interview Protocol (CCIP;
Elliott, 1999) which enquires about changes experienced by the individual since therapy started and helpful and unhelpful aspects of therapy.

Those individuals who proceed to become study participants will be allocated a unique trial code, and all subsequent documents will be referenced by this code to protect participant confidentiality. It is anticipated that the first therapy session for participants in the active condition will typically take place one week after the second assessment appointment with the research team. Prior to each therapy session, participants will be asked to complete the OASIS, ODSIS and any of the three experimental measures (OSSIS, OLSIS, and OFSIS) on which they scored ≥8 at pre-therapy. Post-treatment assessments will take place at week 16 (i.e., as close as possible to 16 calendar weeks from the date of the first session) and 6 months post 16 weeks (as close as possible to 42 calendar weeks from the date of the first session). In addition, where participants finish therapy outside the range of 16 ± 2 weeks (i.e., ≤ 13 weeks, or ≥ 19 weeks), an additional assessment will be carried out post therapy (i.e., as close as possible to the date of the last session). The 16-week, post-therapy and 6-month follow up assessments will consist of administering the ODSIS, OASIS, and CORE-OM (these are administered to all participants), a diagnosis specific measure (selected for each participant on the basis of their primary diagnosis), and any of the three experimental measures (OSSIS, OLSIS, and OFSIS) on which a participant scored ≥8 at pre-therapy. The qualitative interview (CCIP) will be conducted only post-treatment. A summary of the assessments is presented in
Figure 1.

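### The planned between-group comparison at the end of treatment has no named wait-list comparator and adds no valid randomised estimate of EFT-T versus waiting beyond week 16

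*Protocol article*

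**What the plan says.** Under Statistical methods, the main intention-to-treat and per-protocol analyses consist of "within and between groups comparisons at 16 weeks, and the end of treatment". The next sentence applies repeated measures ANOVAs to primary and secondary outcomes at the same two points. The section closes with "The magnitude of between-group effects at 16 weeks and at the end of treatment will also be established".

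The Intervention section limits the life of the control arm: "The delayed intervention, offered to wait-list participants at 16 weeks, will be delivered as per the active intervention described above". Statistical methods agrees ("After 16 weeks, participants from the wait-list will be provided with the active treatment") and says what happens to later data: "pre-post and 6 months follow-up will be assessed for the collated group".

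Two further passages determine when treatment ends. The Intervention section states "Therapy will last 16 to 20 sessions" and lets therapists "extend therapy for up to an additional four sessions if (1) the client continues to be clinically distressed", provided that the client also wishes to continue. Under Client consent process and assessment, the week-16 visit is the post-treatment assessment. An additional one is made only "where participants finish therapy outside the range of 16 ± 2 weeks (i.e., ≤ 13 weeks, or ≥ 19 weeks". The list of primary outcome measures repeats this rule.

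**The concern.** The wait-list is an untreated control only up to week 16. A between-group test at a second, partly later time point needs a comparator, and the article does not say which wait-list measurement that is. The candidates give different estimands. One compares two treated groups. The other sets a fixed week-16 control value against a treated value whose timing varies from client to client and depends partly on how the client is doing.

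What is at stake is the effect size. The Abstract, Objectives and Discussion all say that this trial's estimates should inform the power calculation of a later comparative trial. With the comparator left open, the same data could give a difference near zero or one near the week-16 effect, and the choice could be made after the results are seen.

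**Working it through.** **1. Where end of treatment falls for an EFT-T client** (Client consent process and assessment; primary outcome measures)

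| Therapy ends | End-of-treatment value | Relation to the wait-list's start of EFT-T at week 16 |
|---|---|---|
| Week 13 or earlier | separate assessment | before |
| Weeks 14 to 18 | the week-16 assessment itself | same assessment point as week 16 |
| Week 19 or later | separate assessment | after |

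I take the wait-list's week-16 value as the one recorded before delayed therapy starts. Session frequency is not stated. If sessions are weekly without gaps (assumption), session 16 falls at week 15 and session 20 at week 19. Only clients given the full extension would then reach the late rule. Missed weeks would add others.

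**2. Comparator = each arm's own end of therapy.** Both arms have then had EFT-T. If it works equally well in both, the expected difference is about 0, whatever the effect against waiting.

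**3. Comparator = the wait-list's week-16 value.** Let D16 be the week-16 difference between arms. Let pE and pL be the shares of the EFT-T arm finishing by week 13 and from week 19 on. Let cE and cL be those clients' mean differences between their end-of-therapy and week-16 values. Everyone else has a difference of zero, because the two values are the same record. Hence

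D(end) = D16 + pE × cE + pL × cL.

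- If pE = pL = 0, this is the week-16 test again.
- Otherwise it is the week-16 contrast plus change within the EFT-T arm that has no counterpart in the wait-list. With 20 clients in the arm, each such client shifts the arm mean by 1/20 = 5% of his or her own change.
- The late group is partly selected on outcome, since continuing distress is a condition for extension. Its clients have up to 4 more sessions than the standard 16 (4/16 = 25%).
- The article gives none of pE, pL, cE or cL, so neither the size nor the sign of the added term can be computed.

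A third option, both arms at one later calendar week, fits the article worse. The wait-list would be in therapy, with OASIS and ODSIS taken before sessions but no CORE-OM scheduled at that point.

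**4. Count of tests.** 3 primary outcomes × 2 time points = 6 between-group tests per analysis set, of which 3 carry the end-of-treatment label. Keeping week 16 only leaves 3.

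**5. Sample size** (f = 0.25, power 0.80, alpha 0.05, total 40; Sample size section). Group-by-time interaction with k = 2 groups and m = 2 measurements: λ = f² × N × m / (1 − ρ), with df1 = (k − 1)(m − 1) and df2 = (N − k)(m − 1). The correlation is not stated, so ρ = 0.5 is assumed.

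- N = 34: λ = 0.0625 × 34 × 2 / 0.5 = 8.5, power 0.807.
- Attrition of 15% (assumed; no rate is stated): 34 / 0.85 = 40, the stated figure. Attrition of 10% gives 38 and 20% gives 43.
- At 15% attrition the match depends on ρ: over 0.3 to 0.7, N before attrition runs from 46 down to 22.
- If all 40 are evaluable: λ = 10, power 0.869.

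This calculation uses only pre-therapy and one later measurement, so limiting the between-arm test to week 16 does not change N.

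**6. Illustration of a treated comparator**, N = 40, same formula, by the share of f = 0.25 still present between arms (shares assumed):

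| Share remaining | Power |
|---|---|
| 100% | 0.869 |
| 75% | 0.637 |
| 50% | 0.338 |
| 25% | 0.120 |
| 0% | 0.05 |

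**The case against.** The best defence is that end of treatment and week 16 largely coincide. For anyone finishing in weeks 14 to 18 they are one assessment, made at the point up to which the wait-list is untreated. Early finishers are measured before the wait-list starts therapy. The article also assigns the wait-list's own therapy data to a pooled analysis, which makes the week-16 value the more natural comparator. On that reading the control is untreated, and the fault is limited to timing in a subset of unknown size. The data are described as exploratory, a clean week-16 estimate is planned in any case, and an analysis plan that is not shown might name the comparator.

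Most of this stands, and it rules out a stronger claim that a reader might infer: that half of the between-arm comparisons have no untreated comparator because the wait-list is always in therapy by then. Half is right only as a count of time-point labels. Only clients finishing from week 19 on are measured after the wait-list has been offered EFT-T.

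The defence does not rescue the second time point. Where the two points coincide, the test is a duplicate. Where they differ, the contrast is not concurrent. An analysis plan could choose between the readings, but it could not supply an untreated control after week 16. The article itself states the contrast, so this is not a detail left for later.

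**Conclusion.** The point holds in this limited form. The article commits to between-group tests and effect sizes at the end of treatment without naming the wait-list measurement, and neither available choice adds a valid randomised estimate of EFT-T versus waiting beyond week 16. One choice compares EFT-T with EFT-T. The other repeats the week-16 test, altered by uncontrolled change in clients who finish outside weeks 14 to 18.

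By label, 3 of 6 primary between-group tests per analysis set are involved. The bias cannot be given a figure, because the share finishing outside weeks 14 to 18 is not stated. The power figures for a treated comparator are illustrations that rest on ρ = 0.5 and assumed residual effects, and they do not apply if the wait-list's week-16 value is used. The week-16 comparison is sound on this point, and N = 40 is unaffected.

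**What to change.** In Statistical methods:

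- State that week 16 is the only randomised between-arm comparison.
- Remove the end of treatment from the between-group parts of the section: the main-analysis sentence, the ANOVA sentence and the closing effect-size sentence.
- Report end-of-treatment and 6-month results as within-group change, or as change in the collated group, labelled as uncontrolled.

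If the team wants to keep an end-of-treatment contrast, the least that is needed is to name the wait-list measurement used and call the result descriptive.

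The cost is a change of wording here and in any analysis plan. It needs no new data, visits or participants and leaves the sample size as it is.

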### Randomisation

A random sequence of numbers 1 and 2, corresponding to EFT-T or wait-list, will be generated using an on-line random number generator for each participating therapist, and these lists will be held by a colleague who is independent of, and blind to, the assessment (and allocation to therapist) process. Post SCID-5-RV assessment (see below), the trial manager will allocate participants to the next available therapist, and then request the assignment (either EFT-T or wait-list) for that participant. All assessments will be carried out by a professional other than the therapist. Steps will be taken to ensure week 16, end of therapy, and 6-month follow-up assessments are carried out by professionals blinded to the condition the client is in.

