### Sample size

A sample size of 40 participants was determined (using G*Power –
Faul *et al.*, 2007) on the basis of the comparison between and within the two groups across time, and allowing for research attrition. Moderate effect size (f= 0.25) was used as a determinant of meaningful between groups difference with statistical power of 0.80 and alpha level of 0.05. It is expected that the study is likely to detect change over time within the active treatment (EFT-T) and in-between the active treatment and the wait-list. As the current project is a feasibility study, exploratory use of these initial data should help in planning a definite comparative non-inferiority trial, comparing EFT-T and a standard transdiagnostic CBT.

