### Data management

On referral to the project all potential participants will be given a referral code. Each participant who proceeds to pre-trial assessment by the research team will be given a unique study code which identifies the client as assessed for the study. Participants who proceed from assessment to the trial will then be given a unique trial code, which will identify the client and the corresponding therapist. Paper copies of all measures will be identifiable only by the study and/or trial codes.

All data will be stored in locked filing cabinets in locked offices in the counselling centre and/or the School of Psychology, Trinity College Dublin. All identifying paper data (e.g., GP referral information, signed consent forms; and forms listing participant codes) will be stored in a separate locked filing cabinet to all other anonymised data, and will be accessible only to the Trial Manager and to members of the research team involved in pre-therapy and post-therapy assessments. All audio/video and electronic data will be stored on encrypted hard drives.

In order to mitigate against data entry errors, all data will be double entered into two parallel datasets by two separate members of the research team, and the two datasets will be routinely audited and compared. Multiple imputation will be used for missing data. All regulations set by the Research Ethics Committee at the School of Psychology, TCD, as well as data protection regulations will be observed.

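### At week 16 the repeated-measures ANOVA uses the pre-randomisation baseline only as a change score; an ANCOVA on baseline gives a more precise treatment comparison for one degree of freedom

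*Protocol article*

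**What the plan says.** Statistical methods in the protocol article fixes the method for every primary and secondary outcome: they "will be analysed using repeated measures ANOVAs at 16 weeks and at the end of treatment", and "Effects will be tested at the 0.05 level". No baseline covariate is named.

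The section on client consent and assessment places OASIS, ODSIS and CORE-OM at the first assessment appointment. Randomisation comes later, after the diagnostic interview. The primary-outcome baselines are therefore taken before allocation.

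The Sample size section reads "A sample size of 40 participants was determined (using G*Power" and gives the basis as "on the basis of the comparison between and within the two groups across time". It adds "Moderate effect size (f= 0.25) was used as a determinant of meaningful between groups difference", "with statistical power of 0.80 and alpha level of 0.05". The number of time points, the correlation between them and the attrition rate are not given.

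On allocation, the Randomisation section says that a sequence "will be generated using an on-line random number generator for each participating therapist". It describes no blocking. The Therapists section expects at least five therapists. Wait-list participants are offered therapy only at 16 weeks.

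**The concern.** A baseline measured before randomisation has the same expected value in both arms. Subtracting it in full, as a change score does, is the best use of it only if the regression of the week-16 score on baseline has a slope of 1. At a moderate correlation the slope is well below 1, so the subtraction adds noise and over-corrects any chance baseline difference between the arms.

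This matters more than usual here. The trial has 40 participants, and one of its declared products is a set of effect estimates to inform power calculations for a later comparative trial. Precision of the week-16 difference is part of what the trial is meant to deliver.

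**Working it through.** **Inputs.** From the article: 40 participants, 20 per arm; f = 0.25; power 0.80; alpha 0.05; at least five therapists; therapist-specific lists with no blocking described. Assumed: rho of 0.3, 0.5 and 0.7; two time points (baseline, week 16); equal SD at both times, set to 1; two-sided tests.

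**1. The plan's own figure.** For the group-by-time interaction with two groups and m = 2 time points, the noncentrality is lambda = f² × N × m / (1 − rho), with 1 and N − 2 df. At rho = 0.5 this is 0.0625 × N × 2 / 0.5 = 0.25N. N = 34 gives power 0.807, and 34 / (1 − 0.15) = 40. The stated 40 is therefore reproduced by the interaction test with rho 0.5 and 15% attrition, both assumed. The between-groups main effect would need 98 before attrition, so the interaction is the natural reading. In this layout f = 0.25 equals a difference in change of 1.0 SD.

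**2. Variance of the two analyses.** Per-participant variance is 2(1 − rho) for the change score and 1 − rho² for ANCOVA. The ratio is (1 − rho)(1 + rho) / [2(1 − rho)] = (1 + rho)/2, which is 0.65, 0.75 and 0.85 at rho 0.3, 0.5 and 0.7.

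If the SDs differ (s0 at baseline, s1 at week 16), the change-score variance exceeds the ANCOVA variance by (s0 − rho × s1)². This is never negative, and it is zero only when the slope rho × s1/s0 equals 1.

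**3. Power with 20 per arm and a true difference d = 0.8 SD.** SE = sqrt(2v/20), where v is the variance from step 2. The noncentrality is 0.8/SE. Residual df are 38 for the change score and 37 for ANCOVA.

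| rho | Change score: v, SE, noncentrality, power | ANCOVA: v, SE, noncentrality, power |
|---|---|---|
| 0.3 | 1.40, 0.374, 2.14, 0.549 | 0.91, 0.302, 2.65, 0.733 |
| 0.5 | 1.00, 0.316, 2.53, 0.693 | 0.75, 0.274, 2.92, 0.812 |
| 0.7 | 0.60, 0.245, 3.27, 0.889 | 0.51, 0.226, 3.54, 0.932 |

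At d = 0.5 and rho 0.5, power goes from 0.338 to 0.428. For the plan's own 1.0 SD, the N needed for 80% power falls from 46 to 32, 34 to 26 and 22 to 20 at rho 0.3, 0.5 and 0.7.

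**4. Adding fixed therapist terms.** Simulated power with N = 40, unblocked allocation and no true therapist effect:

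| Setting | Change score | ANCOVA | ANCOVA + therapist |
|---|---|---|---|
| rho 0.5, d 0.8, 5 therapists | 0.68 | 0.79 | 0.74 |
| rho 0.5, d 0.8, 8 therapists | 0.68 | 0.79 | 0.70 |
| rho 0.7, d 0.5, 5 therapists | 0.51 | 0.56 | 0.52 |
| rho 0.7, d 0.5, 8 therapists | 0.51 | 0.56 | 0.47 |

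The therapist terms cost 4 to 9 points. In the last row the full model falls below the planned analysis. The cost is the extra df (four or more) plus chance imbalance of arms within a therapist's small caseload.

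**5. Type I error.** With the same therapist effect in both arms (intraclass correlation, ICC, 0.05), simulated type I error was 0.048 for the change score and 0.045 with the therapist term. With an ICC of 0.1 in treated participants only, it was 0.064 for the change score, 0.076 for ANCOVA and 0.074 for ANCOVA with a common therapist term.

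**The case against.** The strongest defence is that repeated-measures ANOVA is valid, matches the stated sample-size basis and is used in a feasibility trial, so this is a preference about efficiency. That stands as far as validity goes. It does not remove the efficiency loss, which the article itself fixes by naming the method for every outcome.

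A reader might infer four stronger criticisms. The article does not support them.

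- **The baseline is thrown away.** It is not; the interaction uses it as a change score. A group main effect would do much worse, but that is not the contrast that reproduces 40.
- **Leaving out therapist invalidates the standard errors because lists are drawn per therapist.** Unblocked lists force no balance within therapist, so they act like simple randomisation, and type I error holds in step 5. A therapist term is also a detail that an article may leave to a fuller document.
- **A common therapist term would deal with clustering at week 16.** By then only EFT-T participants have been treated by their therapist. Step 5 shows that a term shared by both arms does not repair clustering in one arm. It also shows that ANCOVA is, if anything, slightly more exposed to such clustering than the change score, which is a reason for a sensitivity analysis.
- **The planned ANOVA cannot be combined with the statement that "Multiple imputation will be used for missing data".** With two time points the interaction is a single coefficient and pools by Rubin's rules as an ANCOVA coefficient does.

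**Conclusion.** The point holds as one of efficiency, not validity. For the week-16 comparison the named analysis gives up 15% to 35% of the variance that baseline adjustment would remove, for rho between 0.7 and 0.3. At d = 0.8 that is about 4 to 18 points of power. These figures assume equal SDs at the two times, the same rho in both arms and 20 complete cases per arm. Chance imbalance lowers both powers slightly (0.68 and 0.79 in simulation, against 0.69 and 0.81 at rho 0.5).

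The advantage does not carry over to a model with mandatory fixed therapist effects. How much clustering there is in the EFT-T arm, or in the collated pre-post group, depends on an ICC that the article does not give. The change is worth making but is not essential to a valid trial.

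**What to change.** For the between-group comparison at 16 weeks, replace the repeated-measures ANOVA with an ANCOVA of the week-16 score on arm and the baseline score of the same measure. A mixed model with the baseline mean constrained equal across arms would serve as well. Report the adjusted difference with its 95% confidence interval.

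Do not require therapist as a fixed term in this model. Examine it in sensitivity analyses: as a random effect in the EFT-T arm only at week 16, and as a random effect in the collated pre-post model. Show the results over a range of ICC values.

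The cost is a change of wording and one degree of freedom in the primary model. No new data, visits or participants are needed.
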